### Objectives

#### Primary Objectives

This study aims to investigate the following clinical outcomes: disease progression, in terms of tumor progression (increase in size of existing metastatic lesions with or without the appearance of new metastasis), and the overall survival (OS) in patients who receive *IOCS in combination with LDF* (IOCS-LDF)–processed blood during MSTS. Therefore, this study aims to refute the prevailing conception that cell salvage should be avoided in MSTS owing to concerns of tumor dissemination.

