Patient blood management is an evidence-based, patient-tailored approach aimed at reducing the need for ABT and its associated risks [18]. Patient blood management has both preoperative and perioperative components. Preoperative techniques include patient optimization via cessation of antiplatelet and anticoagulant medications [19,20] and anemia management [18]. Perioperative management comprises achieving surgical hemostasis, reinfusion of intraoperatively salvaged blood, the use of erythropoietic agents, and hemostatic drugs such as tranexamic acid. Randomized [21,22] and nonrandomized [23] studies on the use of IOCS in nononcological surgical procedures indicate that salvaged blood transfusion (SBT) significantly reduces the need for ABT [21-23]. Despite extensive use of SBT in orthopedic, trauma, and cardiac surgical procedures [24], the concern of reinfusion of tumor cells leading to disease progression persists [25-27]. The initial lack of literary evidence on the safety of SBT in oncological surgical procedures has made oncological surgeons reluctant to use SBT in MSTS [25-27].

This reluctance dates to an American Medical Council report from 1986, which stated that SBT was not suitable for use in tumor surgery [28]. This was in turn based on a case report from 1975 where tumor cells were found in salvaged blood [29]. There were concerns that tumor manipulation and resection would result in the spillage of tumor cells into the surgical field [30], which would lead to further metastasis if reinfused via SBT. Recent evidence indicates that circulating tumor cells (CTCs), which are shed by the primary tumor [31], are the most likely cause of tumor metastasis in oncological patients. CTCs have been shown to be eliminated by the reticular endothelial system [32], once they fail to metastasize (unable to complete the process of metastasis). Other CTCs may undergo cellular apoptosis after being retained in the capillary bed or the bone marrow [32]. These host defense mechanisms can prevent metastasis by reducing the metastatic ability of the vast majority of CTCs [33]. Consequently, one can ask, “Can SBT with a limited load of damaged malignant tumor cells cause tumor metastasis and disease progression?”

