### Statistical Analysis

We have defined *disease progression* as the increase in the size of an existing metastatic lesion or the appearance of a new lesion in the lung, liver, or the spinal column, which can be visualized by using radiological imaging.

Demographic and clinical characteristics of patients will be summarized using mean (SD) values for continuous variables with approximately normal distribution, median (IQR) values for continuous variables with skewed distribution, and frequency (percentage) for categorical variables. A 1-way ANOVA will be used to compare the mean of a normally distributed variable across the 3 blood transfusion groups, whereas a Kruskal-Wallis rank test will be used for the comparison of medians. A Fisher exact test will be implemented for categorical variables accounting for potential small frequencies.

The association between individual characteristics and OS will be studied by using the Kaplan-Meier curve and a log-rank test. The crude hazard ratio and its 95% CI will be used to measure the association between individual characteristics and OS and will be calculated based on their original definitions. Multivariate Cox proportional hazard regression will then be used to adjust for statistically significant confounders for the relationship between the type of blood transfusion and OS. The proportional hazards assumption will be tested after the final model is obtained.

The association between the type of blood transfusion and tumor progression will be investigated by the competing risks analysis, taking death without tumor progression as the competing event. First, cumulative incidence curves of the 3 blood transfusion groups will be plotted nonparametrically, and then we will model the relation via a subdistribution hazard regression model. The measure of association will be quantified by the crude subdistribution hazard ratio; its 95% CI and *P* value will be analyzed in a univariate analysis. Subsequently, a multivariate analysis will be used to adjust for potential confounders. All statistical analyses will be done using Stata Special Edition 14.0 (StataCorp LP). The statistical tests will be assumed to be 2-sided, with the conventional 5% significance level.

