#### Analysis of Secondary Outcome Measures

The progression of disease will be assessed using the internationally accepted Response Evaluation Criteria in Solid Tumors (version 1.1) [66,67]. Disease progression is defined as at least a 20% increase in the sum of the diameters of measurable target lesions (eg, lymph nodes and bone metastases with soft tissue components), unequivocal progression of nontarget lesions (eg, malignant ascites or pleural effusions), or the appearance of 1 or more new metastatic lesions.

Computed tomography of chest or abdomen and pelvis will be used to assess metastases in the lymph nodes, lung, liver, or any abdominal organ, all of which can be visualized adequately. Magnetic resonance imaging of whole spine and nuclear medicine bone will also be performed because of their increased sensitivity in detecting early new spinal or skeletal metastases [68]. A lesion identified in a follow-up study in an anatomical location that is not present at baseline is considered a new lesion and will indicate disease progression.

The OS rate will be defined as the proportion of patients who survive until the end of the study period. Median survival times and 95% CI will be estimated using Kaplan-Meier curves for experimental and control groups. The median OS times will be compared using a log-rank test. The survival rate at 6 months after surgery will also be estimated using Kaplan-Meier curves.

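### The study sets out to refute tumour dissemination, but every progression analysis pools new metastases with growth of existing lesions, so a null composite cannot by itself answer that question

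*Protocol article*

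**What the plan says.** **The claim.** Under Primary Objectives the protocol article says that "this study aims to refute the prevailing conception that cell salvage should be avoided in MSTS owing to concerns of tumor dissemination".

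**The feared mechanism.** The Background describes tumour cells spilled during surgery, "which would lead to further metastasis if reinfused via SBT". It also words the worry more broadly: "the concern of reinfusion of tumor cells leading to disease progression persists". The laboratory work summarised there is offered as reassurance that processed cells cannot seed new lesions. The Discussion (Study Findings) names two forms of feared progression, fresh metastases and enlargement of the index lesion.

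**The endpoint.** It is worded in three ways:
- Primary Objectives, repeated under Hypothesis: "tumor progression (increase in size of existing metastatic lesions with or without the appearance of new metastasis".
- Statistical Analysis: "the increase in the size of an existing metastatic lesion or the appearance of a new lesion in the lung, liver, or the spinal column".
- Analysis of Secondary Outcome Measures (RECIST 1.1): "at least a 20% increase in the sum of the diameters of measurable target lesions", or clear progression of nontarget lesions, or any new lesion.

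**The model.** "The association between the type of blood transfusion and tumor progression will be investigated by the competing risks analysis", with death before progression as the competing event. It uses cumulative incidence curves for the three transfusion groups and then a subdistribution hazard regression. A lesion at a site not involved at baseline is identified as new, but it is used only as one way of meeting the progression definition. The article names no outcome or model for new lesions alone.

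**The concern.** Every enrolled patient already has metastatic spine disease. Existing lesions may therefore grow whatever blood is given. In a first-event analysis, a patient whose known lesion grows is counted at that time, and a later new metastasis adds nothing.

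If reinfused cells act mainly by seeding new sites, growth events unrelated to transfusion dilute the contrast between groups. In a superiority trial, dilution toward the null works against the desired claim. Here the hypothesis is absence of added risk and the article states no margin, so dilution works in favour of it. A real increase in new metastases could go unseen while the report says that the dissemination concern has been refuted.

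**Working it through.** **1. Inputs in the document.** The minimum sample is 30 + 30 + 30 = 90. Tests are two-sided at 5%. Follow-up is 4 years or until death. The article gives no effect size, power, margin, progression rate or split between growth and new lesions. The 90 is only the sum of the three groups, and there is no calculation to reproduce.

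**2. Inputs assumed.** Let *p* be the share of the comparator group's progression hazard due to new lesions, *h* the hazard ratio of salvaged blood on new lesions, and *g* its hazard ratio on growth. I take *p* from 0.2 to 0.5 and *h* = 1.5 or 2. The formulas use constant cause-specific hazards. The planned model is for the subdistribution hazard, so they show direction and rough size only.

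**3. Dilution when growth is unaffected (*g* = 1).** Composite HR = 1 + *p*(*h* − 1). The expected z is proportional to ln(HR) × √events, so the ratio of the new-lesion z to the composite z is ln(*h*)√*p* / ln(1 + *p*(*h* − 1)).

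| *h* | *p* | Composite HR | z ratio (new lesions / composite) |
|---|---|---|---|
| 1.5 | 0.2 | 1.10 | 1.90 |
| 1.5 | 0.4 | 1.20 | 1.41 |
| 1.5 | 0.5 | 1.25 | 1.28 |
| 2.0 | 0.2 | 1.20 | 1.70 |
| 2.0 | 0.4 | 1.40 | 1.30 |
| 2.0 | 0.5 | 1.50 | 1.21 |

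Example for *h* = 2, *p* = 0.2: 1 + 0.2 × 1 = 1.20, and 0.693 × 0.447 / 0.182 = 1.70.

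**4. Power with 30 versus 30, *h* = 2, *g* = 1.** Further assumptions are a comparator progression hazard of 1 per time unit, a death hazard of 0.5, follow-up of 2 time units, and new lesions still recorded after growth. Cumulative incidence is (hazard / total hazard) × (1 − exp(−total hazard × 2)). Power is Φ(√(events/4) × ln HR − 1.96).

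| *p* | Composite: events, power | New lesions alone: events, power |
|---|---|---|
| 0.2 | 39, 8% | 18, 31% |
| 0.35 | 40, 16% | 26, 42% |
| 0.5 | 41, 25% | 32, 50% |

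Neither analysis is well powered. Even if all 60 patients in two groups had an event, the HR detectable with 80% power would be exp((1.96 + 0.84)/√(60/4)), about 2.06.

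**5. When growth is also affected.** The composite HR becomes (1 − *p*)*g* + *ph*. The z advantage of new lesions alone disappears when this equals exp(ln(*h*)√*p*), that is, at *g* = (exp(ln(*h*)√*p*) − *ph*)/(1 − *p*):
- *h* = 1.5: *g* is about 1.12, 1.15 and 1.16 for *p* = 0.2, 0.4 and 0.5.
- *h* = 2: *g* is about 1.20, 1.25 and 1.27 for the same *p*. For *p* = 0.5, (1.6325 − 1)/0.5 = 1.265.

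Above these values the composite is the more sensitive endpoint. If *g* = *h*, the z ratio is √*p*, or 0.45 to 0.71.

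**6. The definitions side by side.** Choosing among the three wordings does not remove the problem, because none of them isolates new lesions. Read literally, the wording under Primary Objectives and Hypothesis requires growth, so a new metastasis without growth would not count. The other two wordings do count it. These need to be reconciled in any case.

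**The case against.** Three arguments on the other side carry weight.

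**Growth is itself a stated harm.** The Discussion names index-lesion enlargement alongside new metastasis, and the Background words the worry as disease progression in general. The Background also links allogeneic blood to promotion of tumour growth, and Recruitment expects most salvaged-blood patients to receive some allogeneic blood. Growth is therefore not mere noise. This stands: the composite should be kept, and the dilution figures hold only while any effect on growth is small.

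**Component analyses are usually left to the full protocol or analysis plan.** That is true, and neither is shown. RECIST 1.1 is a recognised definition, and the planned imaging was chosen partly to detect new lesions early. The lack of a component table would be no finding. What remains is that the article itself fixes the claim, the endpoint and the single progression model, and the model does not isolate what the claim is about.

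**A separate outcome has fewer events.** This also stands. A null result on new lesions with 30 per group would be weak evidence of safety.

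A reader might go further and infer that the composite is the wrong endpoint, that the plan is shown to be biased toward a finding of safety, or that only a new-lesion outcome may support the refutation. The documents do not support any of these. They name growth as a harm, they give no event mix from which a bias could be measured, and resting the whole claim on the outcome with fewer events would be debatable.

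**Conclusion.** The point holds in a limited form. The stated aim concerns dissemination, all three progression wordings pool new lesions with growth, and the one planned progression model uses the pooled event. A null composite result therefore cannot by itself show that dissemination did not increase.

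The direction of the dilution depends on salvaged blood acting mainly through new lesions. Under that assumption, with new lesions at 20% to 50% of events, a true hazard ratio of 2 appears as 1.20 to 1.50, and one of 1.5 as 1.10 to 1.25. The size is illustrative because the event mix, the effect and the absence of an effect on growth are all assumed. Once the growth hazard ratio reaches about 1.12 to 1.27, depending on *p* and *h*, the separate analysis no longer has the advantage in sensitivity. It would still be needed to tell the two routes apart.

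**What to change.** Keep composite progression. In Statistical Analysis, add a named safety outcome: time from surgery to first new metastatic lesion, meaning a site not involved at baseline, counted whether or not existing lesions have already grown. Analyse it by transfusion group with cumulative incidence curves and the planned subdistribution hazard regression, taking death without a new lesion as the competing event. Growth of an existing lesion does not end time at risk for this outcome.

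Report the estimate and 95% CI beside those for the composite. State that a null composite result alone will not be described as refuting dissemination. If the full protocol or analysis plan already contains this analysis, it is enough to name it in the article and to limit the claim accordingly.

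**Cost.** One further analysis of lesions already identified against baseline, within the existing 4-year record review. New lesions must go on being recorded after growth has been noted. This depends on standard-of-care imaging, because no research visits are planned, so ascertainment after growth may be incomplete. There will be fewer events and probably a wider CI than for the composite, and the addition does not make 30 per group adequate.

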#### Secondary Objectives

The secondary objectives of the study are to investigate whether reinfusion of IOCS-LDF–processed blood can reduce ABT rates in patients undergoing MSTS. We will also compare the length of stay and overall complication rate of patients who receive salvaged blood and those who receive ABT or no blood transfusion (NBT).

### Hypothesis

The working hypotheses of this study are as follows:

Reinfusion of IOCS-LDF–processed blood of patients undergoing MSTS does not increase the risk of disease progression, in terms of tumor progression (increase in size of existing metastatic lesions with or without the appearance of new metastasis) and OS.Patients receiving IOCS-LDF blood transfusion require less ABT.Patients receiving IOCS-LDF blood transfusion will experience fewer overall complications and shorter length of stay than patients receiving ABT.

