**Results:**

This is the largest clinical study on use of IOCS in MSTS from various primary malignancies to date. It will provide significant clinical evidence regarding the safety and applicability of IOCS in MSTS. It will help reduce use of ABT, improving overall blood management of patients undergoing MSTS. A limitation of this study is that not all patients undergoing MSTS will survive for the follow-up period (4 years), theoretically leading to underreporting of disease progression. Study commenced in 2016 and patient recruitment continued till 2019. As of September 2019, we have collected operative data on 140 patients. However, the 2-year outcomes of about 40.0% (56/140) of patients are in the process of collection. The study is aimed to be published in the years 2023-2024.

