## Methods

### Recruitment

This study aims to recruit a minimum of 90 patients of whom 30 will receive SBT (with or with no allogeneic blood), 30 will undergo ABT, and the remaining 30 will have NBT. From our experience of treating patients with tumor, there are likely to be very few patients who receive only SBT. The majority of patients receiving SBT are likely to receive both SBT and ABT in various proportions. SBT and ABT form the 2 experimental arms, whereas patients with NBT form the control cohort. We will compare the number of patients receiving only SBT with those receiving ABT, if the sample sizes are sufficient.

Patients will be selected from specialist outpatient spine clinics or inpatient wards. These patients may be referred from an inpatient medical oncology team for management, especially in the setting of MSD with cord compression resulting in symptoms such as pain or neurology. A thorough examination of clinical history, physical examination, and review of imaging will be done, and appropriate patient management options will be discussed by the attending orthopedic surgeon. During the enrollment period, whenever a spine surgeon has obtained surgical consent for MSTS in patients with MSD, the principal investigator (NK) will be informed either by a telephone call or by text messaging.

The *research assistant* who is on-site at the National University Hospital during office hours or any member of the research team who is available will interview the patient. During this interview, the interviewer will confirm whether the inclusion criteria are fully met. The study will be explained to suitable subjects, including the advantages as well as possible intra- and postoperative risks of the reinfusion of salvaged blood. A copy of the *patient information sheet and consent form* will be provided to the patient, detailing the recruitment procedures, our objectives, hypotheses, and background information, and any queries will be addressed. Subsequently, written informed consent will be obtained from the patient.

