## Discussion

### Study Findings

This is the largest prospective clinical study on the use of IOCS in MSTS from a variety of primary malignancies. It will provide significant clinical evidence regarding the safety and applicability of IOCS in MSTS. The clinical safety of the use of IOCS has been established in oncological surgical procedures involving gastrointestinal [40], gynecological [41-43], hepatobiliary [40,44-46,55-57], and urological [47-54,58-62] specialties (Multimedia Appendix 1). However, the use of IOCS has neither been studied nor practiced regularly in metastatic musculoskeletal tumor surgeries (MMTSs). This may be because of the skepticism among surgeons about the safety of SBT in MMTSs, despite the presence of substantial supporting evidence in other surgical specialties in the field of oncology [40-54,63,64]. Amidst all the apprehension regarding IOCS, a retrospective comparative review has shown that SBT indeed reduces the need for postoperative ABT [69]. More recently, the use of SBT has been studied prospectively, demonstrating its safety for IOCS in MSTS [70]. Nonetheless, these studies did not have a comparative arm and had a small sample size.

This prospective clinical study is founded on substantiating evidence that salvaged blood is free from viable tumor cells, proven in our earlier methodical basic sciences approach [32,38]. We aim to study the OS, as well as tumor progression in MSTS patients through analysis of their various outcome measures. The results from this approach will help debunk the prevailing myth that IOCS contributes to disease progression either in the form of new metastasis or in the form of an increase in the size of the index lesion.

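### The primary safety hypothesis is absence of harm, but the plan tests for difference at two-sided 5% and sets no bound on its confidence intervals for concluding that risk is not increased

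*Protocol article*

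**What the plan says.** **Claim.** The Hypothesis section of the protocol article states that salvaged blood passed through the leukocyte depletion filter "does not increase the risk of disease progression, in terms of tumor progression" and OS. Primary Objectives makes these two outcomes primary and says the study is meant to *refute* the view that cell salvage should be kept out of metastatic spine tumor surgery. The Discussion (Study Findings) adds: "The results from this approach will help debunk the prevailing myth that IOCS contributes to disease progression".

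**Tests.** Statistical Analysis says: "The statistical tests will be assumed to be 2-sided, with the conventional 5% significance level". For survival, Analysis of Secondary Outcome Measures says: "The median OS times will be compared using a log-rank test". Cox regression gives the adjusted comparison. Progression is analyzed by subdistribution hazard regression, with death without progression as the competing event.

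**Estimates.** Statistical Analysis also says: "The crude hazard ratio and its 95% CI will be used to measure the association between individual characteristics and OS". It plans a 95% interval and P value for the subdistribution HR. No acceptable increase, margin or confidence bound is attached to either measure.

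**Size.** Recruitment sets "a minimum of 90 patients of whom 30 will receive SBT", with 30 more receiving allogeneic blood (ABT) and 30 receiving no transfusion (NBT, the control cohort). The article gives no power or precision rationale. The abstract reports: "As of September 2019, we have collected operative data on 140 patients".

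**The concern.** The conclusion the sponsor wants is the null hypothesis of the planned tests. Failing to reject a null is not evidence for it, and the fewer the events, the more often a test fails to reject. With no other criterion stated, a small or noisy study would look more favorable to the safety hypothesis than a large, precise one.

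This is the primary safety question, asked of patients with metastatic cancer. Broader Implications expects the results to help reduce allogeneic transfusion. If the reassurance came from low power, practice could change on evidence that is still compatible with a material increase in progression or death.

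**Working it through.** **Inputs from the article:** two-sided 5% level; minimum of 30 per group; 140 patients with operative data, split by group not given; follow-up of 4 years or until death.

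**Not in the article, so assumed:** numbers of events and the size of any acceptable increase. For a 30 v 30 comparison I take 30 to 60 events in total. Sixty means that every patient has the event, which is the ceiling. The article gives no calculation behind the 30 per group, so there is no figure of the plan's own to reproduce.

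**Formulas** (two equal groups, unadjusted, D events in total):
- SE(log HR) = 2/√D
- 95% interval at an observed HR of 1 = exp(±1.96 × SE)
- power for a true HR of h = Φ(ln h / SE − 1.96)

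**Worked case, D = 60.** SE = 2/√60 = 0.258. The interval is exp(±0.506) = 0.60 to 1.66. For h = 1.5, ln 1.5 = 0.405, and power = Φ(0.405/0.258 − 1.96) = Φ(−0.39) = 34.8%.

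| Events in the two groups | 95% interval at observed HR 1.0 | Power, true HR 1.5 | Power, true HR 2.0 |
|---|---|---|---|
| 30 | 0.49 to 2.05 | 19.8% | 47.5% |
| 48 | 0.57 to 1.76 | 28.9% | 67.0% |
| 60 (all patients) | 0.60 to 1.66 | 34.8% | 76.6% |
| 93 (140 patients split evenly, nearly all with events) | upper limit 1.50 | 49.8% | 91.7% |

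The last row assumes 140/3, or about 47 patients per group. The even split is an assumption.

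**What a non-significant result would tell us.** If the true HR is 1.0, the test is non-significant 95% of the time. If the true HR is 1.5, it is non-significant in 100 − 34.8 = 65.2% of studies with 60 events and 100 − 19.8 = 80.2% with 30 events. Non-significance is therefore only 95/65.2 = 1.46 or 95/80.2 = 1.18 times as likely under no harm as under a 50% higher hazard. It barely separates the two.

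**What a bound would demand.** With a true HR of 1, one-sided 2.5% and 80% power, events needed = 4 × (1.96 + 0.84)² / (ln margin)². For illustrative margins this gives 191 events at 1.5, 101 at 1.75 and 66 at 2.0. A 30 v 30 comparison cannot yield more than 60. By symmetry, the power columns above are also the chances of excluding a margin of 1.5 or 2.0 when the true HR is 1.

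**The case against.** **Confidence intervals are already planned.** This stands. A reader might infer that only P values are planned, and the article does not support that: it plans HRs and subdistribution HRs with 95% intervals, cumulative incidence curves, and intervals for median survival. For a non-randomized cohort, estimation is a legitimate framework. What is missing is a bound against which to judge the intervals.

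**No sentence equates non-significance with safety.** This also stands. A reader might infer from *refute* and *debunk* that P > 0.05 will be read as proof of safety. The article never says so. The Discussion speaks of *helping* to debunk, Broader Implications acknowledges the observational design and foresees further validation, and Conclusions looks ahead to randomized studies. The defect is that the intended conclusion is announced without a criterion that could establish it.

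**A margin belongs in a fuller document.** This stands in part. The article is condensed, and a numerical margin could sit elsewhere. The two-sided 5% sentence also covers the hypotheses of less ABT and fewer complications, where difference tests fit. But the article itself pairs a no-harm hypothesis with difference testing and states the expected conclusion, so the mismatch is in the text as written.

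**Thirty is a minimum, and 140 patients were enrolled.** True, and it improves precision. Under an even split with nearly all patients having the event, the upper limit at an observed HR of 1 is still about 1.5.

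**Conclusion.** The point holds as a mismatch between the safety hypothesis and the criterion for judging it. At the stated minimum size, a true 50% increase in hazard would go undetected in about 65% of studies even if every patient had the event, and in about 80% with 30 events. The conclusion does not depend on the assumed event rate, because 60 events is the ceiling for 30 v 30.

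The figures are unadjusted and assume equal groups, and applying the formula to the subdistribution HR is an approximation. The quoted intervals apply at an observed HR of 1.0. A reader might take 1.5 to 2 as the smallest increase the study could ever exclude. That does not follow, since an observed HR below 1 would give a lower upper limit.

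**What to change.** Either of two changes resolves it.

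1. **Set a bound.** Base the safety conclusion on the upper limit of the two-sided 95% interval for the adjusted HR (OS) and the adjusted subdistribution HR (progression). Use the article's own contrast with the NBT control and, if wanted, SBT v ABT as an additional stated contrast. Justify the bound clinically, fix it before outcome analysis, and disclose that it was set after recruitment. State that P > 0.05 is not evidence of safety and that an upper limit above the bound is inconclusive.
2. **Or describe the aim as estimation.** Report the precision expected from the actual group sizes and events (unadjusted, at an observed HR of 1), draw no formal safety conclusion, and soften *refute* and *debunk*.

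The cost is analysis wording and a less favorable claim; no extra patients are needed. Under the first option an inconclusive result is likely at the minimum size: with a true HR of 1, a bound of 1.5 would not be excluded in about 65% to 80% of studies. A bound introduced now cannot be presented as part of the original design.
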